### Recruitment

Recruitment was performed at the level of the preschool unit. In the spring of 2016, a meeting took place with preschool managers and preschool unit staff from all preschools in the municipality. They were informed about the study and decided whether they wanted to participate on the basis of the information that was provided to them. All preschool units that expressed interest in participating were included in the study.

Children that fulfilled the eligibility criteria and provided informed consent from their caretakers were then included as participants in each cluster. Neither parents nor preschools received any payment or other incentives in order to participate, but preschool units receive follow-up feedback in terms of the ECERS-3 evaluation. The preschools were also promised continued cooperation with Stockholm University, a collaboration in which further education in the SEMLA or DIL practice would be included, along with a network (already active as the study commenced) in which researchers with findings relating to the preschool setting lectured to interested preschool staff in the municipality on a monthly basis.

### Randomisation

Each cluster was randomly assigned to one of the three conditions with equal probability. If the randomisation resulted in two or more clusters from the same preschool having different intervention assignments (i.e., SEMLA and DIL being assigned to two preschool units within the same preschool), the random assignment was performed again. Randomisation was also performed again if it resulted in obvious skewings in the age distribution across conditions. The randomization was performed in Excel by the first author. Overall, the distribution of children to the three interventions is fairly even (32, 36 and 32%).

Approximately a third of the children participated in the ERP experiment. They were selected based on a randomized priority list. If a child declined to participate or was not present, the next child on the priority list was recorded instead. In sum 139 children (64 boys, 75 girls) were recorded, while 48 children (30 boys, 18 girls) declined to participate, and 21 (13 boys, 8 girls) were not present at the preschool on the day(s) of testing. In 14 cases (3 boys, 11 girls), the priority list was ignored, such that a particularly willing child was recorded to inspire peers.

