### Sample

#### Sample characteristics

The population consists of preschool children in the age range of 48 to 77 months, living in a municipality located in the eastern parts of the Stockholm metropolitan area. The sample consists of 432 children from 28 preschool units, which, in turn come from 18 preschools. Preschool units constitute clusters to which interventions are randomly assigned. Intervention assignment was constrained in the sense that units within the same preschool were always assigned either to the same intervention type or to one of the pedagogical interventions and the control group. From each preschool unit, a smaller group of children was randomly sampled (as described below) for participation in the ERP study. The size of these sub-samples was proportional to the size of the preschool unit from which they were drawn. The sample size in the ERP study is 123 individuals following attrition.

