### RQ1 analyses: Intervention effects

For RQ1 hypotheses, mixed effects modelling will be used to test the null hypotheses that there are no intervention effects on each of the respective outcome variables. Mixed effects modelling allows for the inclusion of multiple hierarchically nested random effects, such as children nested within preschool units and preschool units nested within preschools (e.g., [100]). The mixed effects model can thereby account for systematic influences of preschool units or preschools on the outcome variables. The model formula for the RQ1 hypothesis analyses is:

$$ {\mathrm{POSTSCORE}}_{\mathrm{ijk}}=\kern0.5em {\upalpha}_{0\mathrm{jk}}+{\upalpha}_{00\mathrm{k}}+{\upbeta}_1{\mathrm{INTERVENTION}}_{0\mathrm{jk}}+{\upbeta}_2{\mathrm{Y}}_{\mathrm{ijk}}+{\upbeta}_3{\mathrm{PRESCORE}}_{\mathrm{ijk}}+{\upbeta}_4{\mathrm{FIDELITY}}_{\mathrm{ijk}}+{\upbeta}_5{\mathrm{ECERS}}_{00\mathrm{k}}+{\upvarepsilon}_{\mathrm{ijk},}\ {\upvarepsilon}_{\mathrm{ijk}}\sim \mathrm{N}\left(0,{\upsigma^2}_{\upvarepsilon \mathrm{ijk}}\right),{\upalpha}_{\mathrm{j}}\sim \mathrm{N}\left(0,{\upsigma^2}_{\upalpha \mathrm{j}}\right),{\upalpha}_{\mathrm{k}}\sim \mathrm{N}\left(0,{\upsigma^2}_{\upalpha \mathrm{k}}\right) $$

In the models, the *i*th child is nested within the *j*th preschool unit, which in turn is nested within the *k*th preschool.

These models predict the postscore of the given outcome measure for child *i* as a function of the intervention administered at preschool unit *j*, using the control intervention as the baseline category. They also control for the set of background variables Y of child *i*, as well as the prescore measure of child *i*, centered around zero, as well as the fidelity score for child *i*, as explained in more detail above. Further, they control for the total ECERS rating of preschool *k*, thereby taking into account any influence of preschool quality on the outcome variables. Finally, they include individual intercepts α for each preschool *k*, as well as individual intercepts α for each preschool unit *j*, thereby controlling for systematic differences between preschool units and preschools with respect to the outcome variables.

Separate models will be conducted on selective attention, early maths skills and emotional comprehension, as well as on the composite measures of EF, language and communication.

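### The redraw rule keeps SEMLA and DIL apart but not intervention and control, so allocation is not equal by unit and about half of the control units are expected to share a preschool with an intervention unit

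*Protocol article*

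**What the plan says.** Units are the clusters. Under Sample characteristics: "The sample consists of 432 children from 28 preschool units, which, in turn come from 18 preschools". The number of units in each preschool is not given.

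The Randomisation section states "Each cluster was randomly assigned to one of the three conditions with equal probability" and then gives two reasons for drawing again:

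- **Preschool rule.** The barred pattern is described as "i.e., SEMLA and DIL being assigned to two preschool units within the same preschool), the random assignment was performed again".
- **Age rule.** "Randomisation was also performed again if it resulted in obvious skewings in the age distribution across conditions". No threshold is stated.

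Read alone, the preschool rule might seem to bar every difference within a preschool. Sample characteristics settles it: "units within the same preschool were always assigned either to the same intervention type or to one of the pedagogical interventions and the control group". Control beside SEMLA, or control beside DIL, was an accepted result.

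The RQ1 model estimates each intervention effect "using the control intervention as the baseline category", with all control units in one category. It adjusts for background variables, prescore, fidelity and ECERS, and has random intercepts for preschool and unit. The number of enrolled units per preschool is not among the covariates named in the article.

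**The concern.** The rule protects the contrast between the two interventions and leaves each contrast with control unprotected. It also steers multi-unit preschools towards mixtures of one intervention with control, because the other kind of mixture is discarded.

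Two things are at stake:

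1. **Interpretation of RQ1 against RQ2.** If practice passes from SEMLA or DIL staff to control staff in the same preschool, the RQ1 effects shrink while SEMLA versus DIL hardly moves. The two research questions could then disagree because of the design. The preschool intercept adds to this: the more preschools vary, the more weight the model gives to comparisons within a preschool, which are the exposed ones.
2. **Allocation depends on a variable outside the model.** A unit's chance of control rises with the number of enrolled units in its preschool. If that number is related to outcomes, the contrast of intervention with control is partly confounded by it.

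The power simulation draws 9 clusters per arm separately (27 clusters of 12, so 324 children) and describes no shared preschools, so it does not allow for either effect.

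**Working it through.** Intervention unit means SEMLA or DIL below; control means the BRUK units.

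**1. Probabilities after the preschool rule.** Equal-probability draws that are repeated until accepted are uniform over the permitted patterns, whether the whole list or one preschool is redrawn. For a preschool with m units:

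- permitted patterns: 2^(m+1) − 1
- P(control) = (2^m − 1)/(2^(m+1) − 1)
- P(control and beside an intervention unit) = (2^m − 2)/(2^(m+1) − 1)

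For m = 2, the 9 raw patterns lose SEMLA–DIL and DIL–SEMLA. Of the 7 left, a given unit is control in 3.

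| Enrolled units (m) | P(control) | P(SEMLA) = P(DIL) | P(beside intervention, given control) |
|---|---|---|---|
| 1 | 1/3 = 0.333 | 1/3 | 0 |
| 2 | 3/7 = 0.429 | 2/7 | 2/3 |
| 3 | 7/15 = 0.467 | 4/15 | 6/7 |

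The stated 1/3 per arm is reproduced only for m = 1. It would hold for every m if each preschool received a single condition.

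**2. Totals for 28 units in 18 preschools.** The layout is unknown, so all 42 possible layouts were summed. Two examples:

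- 8 one-unit and 10 two-unit preschools: control 8/3 + 20 × 3/7 = 11.24 units; co-located 20 × 2/7 = 5.71; share 5.71/11.24 = 50.8%.
- 13 one-unit and 5 three-unit preschools: control 13/3 + 15 × 7/15 = 11.33; co-located 15 × 6/15 = 6.0; share 52.9%.

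Over all layouts the average P(control) is 0.399–0.405, so about 40:30:30, and the co-located share is 49.2–53.0%. If the realised unit split was 9/9/10 (an assumption close to the reported 32, 36 and 32% of children), the share is about 57–62%. In the four layouts simulated, the chance of no co-located control unit was 0.05% or less.

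**3. Exposure of RQ1.** Suppose co-located control units take up a fraction c of the intervention effect. The fraction retained is 1 − c × L, where L is the weight that the model puts on co-located controls. L was found by generalised least squares on simulated allocations for the layout of 8 one-unit and 10 two-unit preschools, with 15.4 children per unit (432/28). All variances, c and the two spillover models are assumptions:

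- **Model A:** every co-located control unit takes up c of its neighbour's effect.
- **Model B:** only those beside SEMLA take it up, and the SEMLA effect is tracked.

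| Variance: preschool / unit / child | L, A | A: kept at c = 10, 30, 50% | L, B | B: kept at c = 10, 30, 50% |
|---|---|---|---|---|
| 0 / 0 / 1 | 0.53 | 95, 84, 74% | 0.26 | 97, 92, 87% |
| 0.02 / 0.02 / 0.5 | 0.60 | 94, 82, 70% | 0.35 | 97, 90, 83% |
| 0.05 / 0.02 / 0.93 | 0.64 | 94, 81, 68% | 0.40 | 96, 88, 80% |
| 0.10 / 0.05 / 0.85 | 0.68 | 93, 80, 66% | 0.44 | 96, 87, 78% |

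At c = 0 every entry is 100%.

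**4. Imbalance in number of enrolled units.** Expected share of units that come from multi-unit preschools:

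| Layout | All controls | Interventions | Stand-alone controls |
|---|---|---|---|
| 8 one-unit + 10 two-unit | 76% | 68% | 52% |
| 13 one-unit + 5 three-unit | 62% | 48% | 19% |

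If being in a multi-unit preschool shifted outcomes by 0.2 SD (an assumption), the crude bias would be 0.2 × 0.08 = 0.02 SD to 0.2 × 0.14 = 0.03 SD before adjustment.

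**The case against.** **Spillover is not shown.** A reader might infer that the RQ1 effects are in fact diluted. The article neither states nor quantifies any spillover. It describes trained staff, weekly researcher visits, a SEMLA space set up for the purpose, and DIL play on individual tablets with headphones. This objection stands: exposure is established, dilution is not. The article does warn of a high risk of leakage to testers who spend time at the preschools, so contact between staff of one preschool is a plausible route, but it is not evidence of an effect. For the same reason, a null RQ1 result could not be put down to co-location.

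**The redraw is disclosed.** The sentence on equal probability describes the raw draw, the redraw follows at once, and Sample characteristics says that assignment was constrained. That is fair, and nobody is misled about the mechanism. The probabilities of the accepted allocation are still unequal. With 10 two-unit preschools a raw draw passes the preschool rule only (7/9)^10 = 8% of the time. The even split of children is one realised result with the arms unnamed, and does not restore equal probabilities.

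**Confounding is conditional and small.** Recruitment was by interested unit, so the number of enrolled units is not preschool size, and nothing in the article links it to outcomes. The prescore and the other covariates should absorb part of any effect. This stands as a limit on size.

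**Stand-alone controls are not a clean reference.** The last table shows that they come disproportionately from one-unit preschools, which widens the imbalance. This stands and shapes the fix.

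**The municipality-wide lecture network** might be taken as further contamination. It was open to interested staff everywhere and does not depend on co-location, so it adds nothing here.

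**Conclusion.** The point holds as one of restricted allocation and exposure. The unequal probabilities (1/3, 3/7, 7/15; about 40:30:30) and the expected co-location of 49–53% of control units follow from the stated rule for any layout of 28 units in 18 preschools. They leave out the age redraw, whose effect cannot be computed. They are expectations: the realised number of co-located units is not reported, although the authors should be able to count it.

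The possible loss in RQ1 rests wholly on assumed spillover. It is nil at c = 0. With some variance between preschools, about 93–97% of the effect is kept at 10%, 80–90% at 30% and 66–83% at 50%, the upper ends being where only neighbours of SEMLA are affected. SEMLA versus DIL is largely protected. Confounding by number of enrolled units is possible and probably modest. This is a cheap improvement to how RQ1 can be read, not a demonstrated bias.

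**What to change.** 1. Describe the allocation as restricted, with probabilities that depend on the number of enrolled units per preschool. Report how many control units shared a preschool with a SEMLA or DIL unit.
2. Add number of enrolled units per preschool (1 versus 2 or more) as a fixed covariate in the RQ1 and RQ2 models.
3. Pre-specify an RQ1 sensitivity analysis that splits control into stand-alone and co-located units and keeps the covariate from item 2, because stand-alone controls come disproportionately from one-unit preschools. Report both contrasts with intervals, as support for the primary result and not in its place.

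Fieldwork ended in June 2017, so the design itself cannot change. The article says that the procedures are set out before the data are analysed, so these additions can still be fixed in advance. They use data already held. The cost is one degree of freedom at preschool level and a wider interval for the stand-alone contrast, which is expected to rest on about 5–6 control units (11.24 − 5.71 = 5.5 and 11.33 − 6.0 = 5.3 in the two example layouts).

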#### Age

As age can be expected to be highly predictive of all of the outcome measures, the age of the children in months was used as a control predictor.

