### RQ3 analyses: Mediating effects

Hypotheses regarding mediating effects are tested on the basis of the method proposed by Preacher & Hayes [101]. Preacher & Hayes [101] differentiate between the *total effect* of X on Y, which is the effect when not taking into account the mediator M, the *direct effect* of X on Y, the effect when the mediator is taken into account, and the *indirect effect* of X on Y, the effect of X on Y as mediated by M. In order to estimate the indirect effect, Preacher & Hayes [101] propose a method of fitting the following three regression models:

Y_i_ = α + cX_i_ + ε_i_ where *c* estimates the total effect

M_i_ = α + aX_i_ + ε_i_ where *a* estimates the effect of X on the mediator M

Y_i_ = α + c’X_i_ + bX_i_ + ε_i_ where *c’* estimates the direct effect of X on Y and *b* the effect of M on Y when controlling for X

A prerequisite for a mediation effect is that c is significant (that is, that there is an effect of X on Y at all, that a is significant (that is, that there is an effect of X on M), and that b is significant (that is, there is an effect of M on Y over and above that of X).

The indirect effect, that is, the mediation effect, is equal to the product of a and b, *ab*, which in most cases is equivalent to the difference between c and c’. Several ways of calculating the standard error of ab have been proposed (e.g., [102, 103]; and see [104], for a review). However, following Preacher & Hayes [101], the standard error and significance of ab is calculated on the basis of bootstrapping. Here, ab is calculated on the basis of 10,000 bootstrap samples, yielding a distribution of 10,000 ab estimates. The point estimate of ab is simply the mean of that bootstrapped distribution, the standard error is the standard deviation of the distribution, and the confidence interval is the 5 and 95% percentile of the distribution. The bootstrapped *p* value of ab is the proportion of ab estimates that is equal to or lower than zero and the total number of ab estimates.

In order for a null hypothesis of no mediation effect to be rejected, the effects of a, b, c and ab, as estimated on the basis of bootstrapping, need to be significant.

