### RQ4 analyses: Moderating effects

RQ4 hypotheses concern moderating effects, that is, hypotheses regarding whether the strength of an observed intervention effect on an outcome variable depends on another variable. In other words, RQ4 hypotheses involve hypotheses regarding interaction effects between interventions and other variables. These hypotheses are also tested with mixed effects modelling.

Firstly, we hypothesize that both the SEMLA and DIL intervention effects on selective attention, EF score, Language score and TEC will be negatively moderated by SES. That is, the intervention effects should be stronger on low-SES children than they are on high-SES children. These negative SES moderation hypotheses are tested with the model

$$ {\mathrm{POSTSCORE}}_{\mathrm{ijk}}=\kern0.5em {\upalpha}_{0\mathrm{jk}}+{\upalpha}_{00\mathrm{k}}+{\upbeta}_1{{\mathrm{INTERVENTION}}_{0\mathrm{jk}}}^{\ast }\ {\upbeta}_2{\mathrm{SES}}_{\mathrm{ijk}}+{\upbeta}_3{\mathrm{PRESCORE}}_{\mathrm{ijk}}+{\upvarepsilon}_{\mathrm{ijk},}\ {\upvarepsilon}_{\mathrm{ijk}}\sim \mathrm{N}\left(0,{\upsigma^2}_{\upvarepsilon \mathrm{ijk}}\right),{\upalpha}_{\mathrm{j}}\sim \mathrm{N}\left(0,{\upsigma^2}_{\upalpha \mathrm{j}}\right),{\upalpha}_{\mathrm{k}}\sim \mathrm{N}\left(0,{\upsigma^2}_{\upalpha \mathrm{k}}\right) $$

These models predict the postscore for child *i* as a function of the interaction between the intervention at preschool unit *j* and the SES score for child *i* while controlling for the prescore measure of child *i*, centered around zero. They also include individual intercepts α for each preschool *k* and for each preschool unit *j*, thereby controlling for differences between preschool units and preschools.

Secondly, both the SEMLA and DIL intervention effects on EF are hypothesized to be negatively moderated by the EF score at pretesting. In other words, the intervention effects on EF should be stronger on low-EF children than on high-EF children. This negative EF moderation hypothesis is tested with the model

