### RQ1 and RQ2 analyses: Intervention effects and intervention differences

Since RQ2 hypotheses regarding intervention differences will be tested on the basis of planned comparisons testing differences between the intervention effects in the RQ1 hypothesis models, RQ1 and RQ2 analyses will be tested together. As mentioned above, we will apply p-value correction to the p-values of coefficients that address the hypotheses.

Table 4 shows the statistics for the intervention model coefficients, including the planned comparisons of the intervention differences, for all RQ1 and RQ2 models. These models test intervention effects and intervention differences on EF, Language, Math and TEC. Apart for the SEMLA intervention effect on EF score and the DIL intervention effect on TEC, these analyses’ power show strong power for all intervention effects and intervention differences under the assumed effect sizes (see Table 3). Notably, the Beta coefficient for the SEMLA intervention on math is negative, indicating that SEMLA in fact might have a negative effect on early maths skills.

**Table 4 Tab4:** Simulation statistics for the intervention model coefficients of all RQ1 and RQ2 models

Statistic	EFScore			Language Score			Math			TEC		
	DIL	SEMLA	DIL vs. SEMLA	DIL	SEMLA	DIL vs. SEMLA	DIL	SEMLA	DIL vs. SEMLA	DIL	SEMLA	DIL vs. SEMLA
Mean Beta	0.85	0.30	0.55	0.49	1.06	−0.57	0.10	−0.08	0.18	0.02	0.75	−0.73
Beta.lower	0.55	−0.03	0.22	0.21	0.78	−0.87	0.06	−0.14	0.11	−0.50	0.31	−1.18
Beta.upper	1.16	0.64	0.82	0.77	1.34	−0.28	0.13	−0.02	0.25	0.98	1.67	−0.31
boot.p	.000	.036	.000	.000	.000	.000	.000	.003	.000	.584	.002	.002
mean.p	.000	.096	.003	.008	.000	.003	.003	.029	.000	.424	.018	.022
p.lower	.000	.000	.000	.000	.000	.000	.000	.000	.000	.000	.000	.000
p.upper	.000	.774	.036	.080	.000	.033	.022	.326	.000	.971	.157	.195
Power	1.00	0.69	0.98	0.96	1.00	0.99	0.99	0.89	1.00	0.17	0.91	0.89
adj. p mean	.000	.118	.005	.010	.000	.001	.004	.038	.000	.472	.026	.031
adj. p.lower	.000	.000	.000	.000	.000	.000	.000	.000	.000	.000	.000	.000
adj. p.upper	.000	.816	.062	.130	.000	.050	.037	.408	.000	.975	.214	.252
adj. Power	1.00	0.61	0.97	0.94	1.00	0.97	0.98	0.86	1.00	0.16	0.87	0.85

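### The RQ3 mediation and RQ4 moderation models omit age, although the plan calls age strongly prognostic and adjusts for it in RQ1 and RQ5

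*Protocol article*

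**What the plan says.** Under Randomisation, the article states: "Randomisation was also performed again if it resulted in obvious skewings in the age distribution across conditions". The Age section names age in months as a control predictor because "age can be expected to be highly predictive of all of the outcome measures". The sample spans 48 to 77 months (Sample characteristics).

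The article prints its model equations, so it is visible where age is used:

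- **RQ1.** The text under the equation says: "They also control for the set of background variables Y of child". Age belongs to that set.
- **RQ2.** The contrasts are "planned comparisons testing differences between the intervention effects in the RQ1 hypothesis models", so they inherit the adjustment.
- **RQ5.** The equation carries Y.
- **RQ3.** The article follows a published mediation method whose authors "propose a method of fitting the following three regression models". These contain the intervention and the mediator and nothing else. "The indirect effect, that is, the mediation effect, is equal to the product of a and b".
- **RQ4.** The SES model uses the intervention-by-SES term "while controlling for the prescore measure of child", plus unit and preschool intercepts. The ECERS model has the same form. The EF model has only the intervention-by-EF-prescore term and the intercepts.

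No sentence adds age or Y to RQ3 or RQ4.

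**The concern.** The plan treats age as important enough to steer allocation and to adjust the main analyses, then leaves it out of two families of hypothesis tests without giving a reason.

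The consequence differs between the two. In RQ3 the intervention is randomised but the mediator is not. Older children are likely to score higher on both the mediator and the outcome, so part of the mediator-outcome association can be due to age. Balancing age across arms does nothing about this, because the confounding operates between children within arms. Path b, and with it ab, may then reflect maturation rather than mediation.

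In RQ4 the issue is efficiency: a prognostic baseline variable is left in the residual.

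**Working it through.** **1. Term check.**

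| Analysis | Terms printed besides intervention | Age adjusted? |
|---|---|---|
| RQ1 | Y, prescore, fidelity, ECERS, unit and preschool intercepts | Yes, through Y |
| RQ2 | Contrasts from the RQ1 models | Yes |
| RQ3 (three regressions) | Mediator only, in the third | No |
| RQ4, SES | SES interaction, prescore, intercepts | No |
| RQ4, EF | EF prescore interaction, intercepts | No |
| RQ4, ECERS | ECERS interaction, prescore, intercepts | No |
| RQ5 | Y, time, fidelity, ECERS, intercepts | Yes, through Y |

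The third RQ3 regression prints the intervention twice. I read the second as the mediator, as the accompanying text describes. The article gives no figure for age correlations, so the sizes below rest on assumed values.

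**2. RQ3 with level or post scores.** If the true b is 0 and age is unrelated to arm, the spurious standardised b = r(age, M) × r(age, Y). The chance that it is significant follows from Fisher's z with n = 432, two-sided alpha 0.05 (the article gives 0.05 but not the sidedness) and independent children.

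| Assumed r, both variables | Spurious b | Chance that b is significant |
|---|---|---|
| 0.3 | 0.09 | 0.46 |
| 0.4 | 0.16 | 0.92 |
| 0.5 | 0.25 | 1.00 |
| 0.6 | 0.36 | 1.00 |

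Example: atanh(0.09) × √429 = 0.0902 × 20.71 = 1.87, and P(Z > 1.96 − 1.87) ≈ 0.46.

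**3. RQ3 with difference scores.** Table 1 names a difference as the measure for every RQ3 outcome. With equal SDs, r(age, difference) = [r(age, post) − r(age, pre)] / √[2(1 − r(pre, post))].

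- If age correlates equally with pre and post, this is 0.
- If the two correlations differ by 0.05 to 0.10 and the pre-post correlation is 0.6 to 0.8 (assumed), it runs from 0.05/√0.8 = 0.056 to 0.10/√0.4 = 0.158.
- Mediator and outcome both differences: spurious b is 0.056² = 0.003 to 0.158² = 0.025, significant in 5 to 8% of trials.
- Mediator a level score with age correlation 0.5, outcome a difference: spurious b is 0.5 × 0.056 = 0.03 to 0.5 × 0.158 = 0.08, significant in 9 to 38%.

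**4. From a spurious b to a mediation claim.** The RQ3 section requires a, b, c and ab all to be significant, so the figures in steps 2 and 3 are not false-claim rates. The gate gives little protection where the intervention truly affects both mediator and outcome. A simulation on level scores (3000 runs, two arms, n = 290, independent children, effects of 0.4 SD on mediator and outcome, true b = 0, all assumed) found a, b and c jointly significant in 29%, 66%, 87% and 87% of trials for r = 0.3, 0.4, 0.5 and 0.6. With age added, the rate was 4 to 5%. The test of ab was not included and would lower the unadjusted rates.

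**5. RQ4.** The standard error is multiplied by √(1 − R²), where R² is the share of the variance left after the prescore that age explains. For R² = 0.02 this is √0.98 = 0.990; for 0.10 it is √0.90 = 0.949. The saving is about 1 to 5%. A simulation of treatment contrasts with 28 units, 432 children and allocation constrained on age points the same way. With the prescore in the model, adding age moved power from 0.87–0.88 to 0.88–0.90, and type I error from 0.042–0.051 to 0.045–0.060. It did not cover the interaction terms that RQ4 tests.

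**The case against.** Several points on the other side have force.

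- **Table 1 names difference scores for RQ3.** This stands, and it shrinks the bias sharply (step 3). It is not conclusive: Table 1 uses the same label for RQ1, whose equation models the postscore, and the RQ3 equations do not define their variables as differences. The communication ratings were made from posttest sessions only (Measures of communication), so no difference can be formed for that component.
- **The direction of bias is not fixed.** This stands for gains, where a ceiling on one test and growth on another could give age correlations of opposite sign.
- **A significant b is not a mediation finding.** This stands. A reader might infer from step 2 that false mediation claims would occur in 46 to 100% of trials. The documents do not support that, because a, c and ab must also be significant.
- **The redraw is beside the point for RQ3.** This stands. A reader might infer that redrawing on age creates the confounding or invalidates the tests. Age would confound the mediator-outcome path under any allocation. For treatment contrasts, ignoring a variable that constrained allocation tends to make tests conservative rather than liberal, and the RQ1 and RQ2 contrasts are adjusted anyway.
- **The article is condensed and the RQ3 equations are generic.** This carries some weight for RQ3. It is weak for RQ4, whose equations are specific, and Y is printed wherever it is used.
- **The RQ4 models have a prescore or EF prescore and random intercepts.** This stands. They absorb much of the age effect, so the loss there is small.

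**Conclusion.** The point holds in a limited form. Age is declared strongly prognostic and is adjusted for in RQ1, RQ2 and RQ5, but it is absent from every printed RQ3 and RQ4 model.

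In RQ3 the omission can bias b and ab. The bias is probably upward and possibly large if level or post scores are analysed (spurious b of 0.09 to 0.36 for assumed age correlations of 0.3 to 0.6). It is much smaller and of uncertain sign for difference scores (about 0.003 to 0.08 in size under the assumptions in step 3). It becomes a false mediation claim only when a, c and ab are also significant, which is most plausible where the intervention really does affect both variables.

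In RQ4 the stake is precision alone, about 1 to 5% in standard error if age explains 2 to 10% of the variance left after the prescore. All these sizes depend on assumed correlations and, for RQ3, on independent children. The RQ1 and RQ2 analyses are not affected.

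**What to change.** Add age in months to the mediator and outcome models of RQ3 and to all three RQ4 models, as RQ1 already does. State whether the RQ3 variables are post scores or differences, since the size of the problem turns on that.

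Age is already collected and already used as a covariate, so the analysis cost is one extra term per model. The simulated power in Tables 5 and 6 describes the models as printed and would strictly need rerunning.

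Adding the rest of Y is optional. It would cover other mediator-outcome confounders, but the background data come from parent and preschool questionnaires, so children with incomplete forms could be lost.
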